A study by Go et al., reviewed outcome data (11,526 subjects) in a large primary care setting and confirmed that thromboembolic risk increases progressively with CHADS2 score. The study also noted that oral anticoagulation with warfarin reduces the risk of stroke in most subjects with the exception of those at lowest risk (CHADS2 score of zero) and highest risk (CHADS2 ≥ 5) for stroke.

In a meta-analysis conducted by Andersen et al., warfarin was found to be superior to aspirin and placebo in reducing the risk of both stroke and systemic embolism in subjects with NVAF. Hart et al. reported that adjusted dose warfarin reduces stroke by 64% (6 trials) and antiplatelet agents reduce stroke risk by 22%. The study also reported that risk of intracranial hemorrhage was doubled with adjusted dose warfarin compared with aspirin, although the absolute risk increase was by adjusted-dose warfarin vs. control.

Subjects are often poorly compliant with anticoagulation, and anticoagulants are contraindicated in selected subsets of subjects. The reasons given for being contraindicated included prior bleed, patient refusal/preference, high bleeding risk, frequent falls/frailty, need for dual antiplatelet therapy, unable to adhere/monitor warfarin, comorbid illness, prior intracranial hemorrhage, allergy, occupational risk and pregnancy.

*\*See Appendix A for a listing of abbreviations used throughout this document*

Recently, new drugs have been developed with less dietary and pharmacological interactions and less stringent requirements for frequent INR monitoring. Major trials such as RE-LY and ROCKET AF demonstrated that dabigatran and rivaroxiban are non-inferior to warfarin in the prevention of stroke and systemic embolism. The ARISTOTLE Trial demonstrated apixaban was superior to warfarin in preventing stroke or systemic embolism, caused less bleeding, and resulted in lower mortality in subjects with atrial fibrillation. The ENGAGE AF-TIMI 48 Trial demonstrated both once-daily regimens of edoxaban were noninferior to warfarin with respect to the prevention of stroke or systemic embolism and were associated with significantly lower rates of bleeding and death from cardiovascular causes.

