## **8. SERIOUS ADVERSE EVENTS, SERIOUS ADVERSE DEVICE EFFECTS, DEATHS AND DEVICE DEFICIENCIES**

Risks associated with the Amulet device are similar to other implantable cardiac occlusion devices. Some of the potential risks include but are not limited to those listed below. The definitions noted below are used for the purposes of this study. Radiation risks associated with the procedure are comparable to a diagnostic catheterization procedure.

Only serious adverse events (SAEs) will be collected for this study. Serious adverse events are classified as serious adverse events or serious adverse device effects (SADEs). A planned hospitalization for a pre-existing condition is not considered a serious adverse event.

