### **8.1 Serious Adverse Events**

A serious adverse event is an adverse event that led to:

- Death
- A serious deterioration in the health of the subject, that either resulted in:
  - A life-threatening illness or injury OR
  - A permanent impairment to a body structure or a body function OR
  - An in-patient or prolonged hospitalization OR
  - A medical or surgical intervention to prevent life-threatening illness or injury or permanent impairment to a body structure or a body OR
  - A malignant tumor OR
  - Fetal distress, fetal death or a congenital abnormality or birth defect

Potential serious adverse events include but are not limited to:

- **Air Embolus** – symptomatic event resulting from the introduction of air into the circulatory system
- **Allergic reaction** – idiosyncratic reaction to the device implanted or to nickel
- **Anesthesia reaction** – undesired reaction to anesthetic agent
- **Arrhythmia** – cardiac rhythm disturbance
- **Bleeding** – *\*see definition of bleeding as defined by BARC at end of section*

- **Cardiac arrest** – failure of the heart to contract
- **Cardiac tamponade** – constriction of the heart causing inefficient contraction resulting from accumulation of excess fluid in the pericardium
- **Death** – permanent cessation of all vital bodily functions
- **Device embolization** – movement of the device from its intended location
- **Device migration** – movement of the device within its intended location
- **Embolic event** – acute vascular insufficiency or occlusion of the extremities or any non-central nervous system organ associated with clinical, imaging, surgical/autopsy evidence of arterial occlusion in the absence of other likely mechanism (e.g., trauma, atherosclerosis, or instrumentation). When there is presence of prior peripheral artery disease, angiographic or surgical or autopsy evidence is required to show abrupt arterial occlusion
- **Fever** – defined as a body temperature  $> 37.5$  or  $38.3$  °C ( $99.5$  or  $100.9$  °F)L
- **Foreign body embolization** – movement of device material, delivery system material, or other material from its intended location
- **Hypotension** – sustained systolic blood pressure  $< 90$  mmHg
- **Hypertension** – systolic blood pressure of  $> 160$  mmHg
- **Infection** – invasion and growth of a pathogenic organism within the body

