**\*Bleeding**

Classified as Type 0 – 5 according to the following BARC definitions:

**Type 0**: No bleeding

**Type 1**: Bleeding that is not actionable and does not cause the patient to seek unscheduled performance of studies, hospitalization, or treatment by a healthcare professional; may include episodes leading to self-discontinuation of medical therapy by the patient without consulting a healthcare professional

**Type 2 (minor)**: Any overt, actionable sign of hemorrhage (e.g. more bleeding than would be expected for a clinical circumstance, including bleeding found by imaging alone) that does not fit the criteria for Type 3, 4, or 5 but does meet at least one of the following criteria: (1) requiring nonsurgical, medical intervention by a healthcare professional, (2) leading to hospitalization or increased level of care, or (3) prompting evaluation

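### The serious adverse event exemption for planned admissions has no limit on timing or worsening, conflicts with the Section 8.1 definition, and can leave some late events and bleeds unreported

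*Protocol*

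**What the plan says.** The introduction to protocol Section 8 sets the scope of collection: "Only serious adverse events (SAEs) will be collected for this study". In the same paragraph it adds an exemption: "A planned hospitalization for a pre-existing condition is not considered a serious adverse event". No other section limits that exemption by when the admission was planned or by whether the condition had worsened.

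Section 8.1 defines a serious adverse event as an adverse event that led to death or to this: "A serious deterioration in the health of the subject, that either resulted in" one of several alternative outcomes. Two of them matter here: "An in-patient or prolonged hospitalization OR" and, separately, "A medical or surgical intervention to prevent life-threatening illness or injury or permanent impairment". Life-threatening illness or injury and permanent impairment are further alternatives.

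Bleeding is on the Section 8.1 list of potential serious adverse events, graded by BARC type ("see definition of bleeding as defined by BARC at end of section"). One of the ways to reach type 2 is "leading to hospitalization or increased level of care". Type 3a is met by transfusion or by a haemoglobin drop, with no reference to admission.

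Section 4.3.1 makes late serious adverse events through 2 years (objective 2) and the percentage of bleeding events through 2 years (objective 4) primary. Section 12 reports both as simple proportions with exact 95% confidence intervals and tests no hypothesis.

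**The concern.** An exemption for elective admissions normally serves to keep prearranged care for stable disease out of the event count. As worded, this one reaches further. A site applying it literally may treat an admission arranged in, say, month 14, because a known condition had got worse, as exempt. Section 8.1 would call the same episode a serious adverse event.

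The conflict matters because nothing downstream repairs it:

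- Non-serious events are not collected, so there is no wider dataset to search.
- The clinical events committee adjudicates reported events (Sections 3.6 and 13.2) and cannot see the others.
- Monitoring is centralized, with on-site visits at the sponsor's discretion (Section 10). The source verification in Section 6.5 compares submitted results with originals.
- An analysis plan cannot restore data that were never recorded.

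Pre-existing disease is universal in this study, since every subject has atrial fibrillation, and the baseline HAS-BLED score records bleeding or a predisposition to it (Section 6.1). Any loss runs in one direction, towards lower primary percentages.

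**Working it through.** **Step 1. The two rules side by side.** The protocol states no figure that depends on the exemption, so there is nothing to reproduce. The check is how the two rules classify the same event.

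| Event during follow-up | Section 8.1 definition | Section 8 exemption, read literally |
|---|---|---|
| Prearranged admission, stable condition | Not serious (no deterioration) | Exempt; the rules agree |
| Unplanned admission for serious deterioration | Serious | Does not apply; the rules agree |
| Deterioration that is life-threatening, causes permanent impairment, or needs intervention to prevent either; admission scheduled | Serious, whatever the admission status | Removes the hospitalization criterion only; still serious |
| Serious deterioration of a pre-existing condition, in-patient admission scheduled during follow-up, no other criterion met | Serious | Exempt; **the rules conflict** |

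Only the last row is exposed. Some BARC type 2 bleeds from a known source, and some type 3a bleeds that are not life-threatening, could fall there. BARC type grades a bleed; it is not itself one of the Section 8.1 seriousness criteria.

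**Step 2. Direction.** Let x be the subjects with an event, N the Section 12 denominator (subjects with the event plus all others reaching 2 years), and k the subjects whose only event is missed.

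- If the missed subjects reach 2 years, the reported proportion is (x − k)/N.
- If they do not, they leave numerator and denominator alike: (x − k)/(N − k).

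Both are below x/N whenever 0 < k ≤ x < N, so any loss lowers the percentage.

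**Step 3. Illustration of size. All rates here are assumptions.** The protocol gives neither a bleeding rate nor a share of events that might be exempted. Take N = 1000 (the planned enrolment, all in the denominator), a true 2-year bleeding proportion p of 10% or 20%, and a share f of bleeders lost of 5%, 15% or 20%. Then k = 1000 × p × f. Intervals are Clopper-Pearson 95%.

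| p | f | k | Reported | Exact 95% CI | Contains p? |
|---|---|---|---|---|---|
| 10% | 0 | 0 | 10.0% | 8.2–12.0% | yes |
| 10% | 5% | 5 | 9.5% | 7.8–11.5% | yes |
| 10% | 15% | 15 | 8.5% | 6.9–10.4% | yes |
| 10% | 20% | 20 | 8.0% | 6.4–9.9% | no |
| 20% | 0 | 0 | 20.0% | 17.6–22.6% | yes |
| 20% | 5% | 10 | 19.0% | 16.6–21.6% | yes |
| 20% | 15% | 30 | 17.0% | 14.7–19.5% | no |
| 20% | 20% | 40 | 16.0% | 13.8–18.4% | no |

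At a 5% loss the shift (0.5 or 1.0 percentage points) is well inside the interval half-width of roughly 1.9 or 2.5 points. It reaches or exceeds the half-width only when the assumed loss is large. The denominator matters too: if the 30 missed subjects in the 20%/15% row had not reached 2 years, the result would be 170/970 = 17.5% (CI 15.2–20.1%), which contains 20%.

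**The case against.** The strongest reply is that the exemption names a hospitalization, not the adverse event behind it. An ordinary reader would take it to mean that an elective admission for known disease is not serious in itself, while a real deterioration is still judged under Section 8.1. A recurrent bleed can also be seen as a new event, with only the source lesion pre-existing. If treatment was needed to prevent life-threatening illness, the intervention criterion applies without any admission.

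Much of this stands. A reader might infer that all worsening disease treated by scheduled admission, or all recurrent bleeding from a known source, is excluded from objectives 2 and 4. The documents do not support that, because the other alternatives in Section 8.1 are untouched. Nor do they support a claim that hospitalization is often the only criterion met for type 2 and type 3a bleeds; no section says so.

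Evidence on the population is also limited. Section 2 observes that "The reasons given for being contraindicated included prior bleed, patient refusal/preference, high bleeding risk, frequent falls/frailty", but this is background on selected subsets of patients. The inclusion criteria in Section 4.4.1 require neither a prior bleed nor a contraindication to anticoagulation.

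The case report forms are under separate cover, and the clinical events committee may refine event definitions (Section 13.2), so a limit may exist elsewhere. That does not settle the matter: the protocol is the governing text, and the committee cannot adjudicate an event that a site considered exempt and never sent.

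What the reply does not remove is the last row of the first table. There, the reasonable reading and the literal one give different answers, and the protocol does not choose between them.

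**Conclusion.** The point holds as an over-broad stated rule that conflicts with the protocol's own definition. It is not a wholesale exclusion of deteriorations or bleeds. The exposed set is narrow: events whose sole seriousness criterion is an in-patient admission scheduled during follow-up for a pre-existing condition that has worsened. For these, under-reporting in objectives 2 and 4 is possible, would lower the percentages, and could not be recovered after collection.

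The size cannot be estimated from the protocol and is probably small. A reader might take a 3-point understatement from the 20%/15% row as the expected bias. It is not: it needs a high assumed event rate, a high assumed loss and every missed subject reaching 2 years. Within an assumed loss of 5% to 15%, it is the only combination of extremes whose interval excludes the true rate. A reader might also infer that the bias differs between sites according to admission practice. That is plausible with up to 75 sites, but nothing in the document demonstrates it.

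No stated sample size, hypothesis or interval method is affected. The change is worth making because the lost information is irretrievable and the correction is one short edit.

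**What to change.** Replace the exemption in Section 8 with a limited one along these lines: a hospitalization already planned before introduction of the dilator/delivery system, for a pre-existing condition that has not seriously deteriorated since then, is not by itself a serious adverse event; the underlying adverse event is still assessed against all Section 8.1 criteria. Introduction of the dilator/delivery system is the natural reference point because Section 8.1.2 starts safety surveillance there. Carry the same wording into the case report form completion instructions.

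The cost is a short edit to Section 8 and those instructions, slightly more event forms for sites and the events committee, and slightly higher reported percentages for late serious adverse events and bleeding. No visit, treatment, sample size or analysis method changes.

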### **8.1 Serious Adverse Events**

A serious adverse event is an adverse event that led to:

- Death
- A serious deterioration in the health of the subject, that either resulted in:
  - A life-threatening illness or injury OR
  - A permanent impairment to a body structure or a body function OR
  - An in-patient or prolonged hospitalization OR
  - A medical or surgical intervention to prevent life-threatening illness or injury or permanent impairment to a body structure or a body OR
  - A malignant tumor OR
  - Fetal distress, fetal death or a congenital abnormality or birth defect

Potential serious adverse events include but are not limited to:

- **Air Embolus** – symptomatic event resulting from the introduction of air into the circulatory system
- **Allergic reaction** – idiosyncratic reaction to the device implanted or to nickel
- **Anesthesia reaction** – undesired reaction to anesthetic agent
- **Arrhythmia** – cardiac rhythm disturbance
- **Bleeding** – *\*see definition of bleeding as defined by BARC at end of section*

- **Cardiac arrest** – failure of the heart to contract
- **Cardiac tamponade** – constriction of the heart causing inefficient contraction resulting from accumulation of excess fluid in the pericardium
- **Death** – permanent cessation of all vital bodily functions
- **Device embolization** – movement of the device from its intended location
- **Device migration** – movement of the device within its intended location
- **Embolic event** – acute vascular insufficiency or occlusion of the extremities or any non-central nervous system organ associated with clinical, imaging, surgical/autopsy evidence of arterial occlusion in the absence of other likely mechanism (e.g., trauma, atherosclerosis, or instrumentation). When there is presence of prior peripheral artery disease, angiographic or surgical or autopsy evidence is required to show abrupt arterial occlusion
- **Fever** – defined as a body temperature  $> 37.5$  or  $38.3$  °C ( $99.5$  or  $100.9$  °F)L
- **Foreign body embolization** – movement of device material, delivery system material, or other material from its intended location
- **Hypotension** – sustained systolic blood pressure  $< 90$  mmHg
- **Hypertension** – systolic blood pressure of  $> 160$  mmHg
- **Infection** – invasion and growth of a pathogenic organism within the body
- **Multi-Organ Failure** – the failure of two or more systems, such as the cardiovascular and renal systems, and is a common consequence of sepsis (the presence of bacteria in the blood) and of shock (very low blood pressure)
- **Myocardial infarction (heart attack)** – the death of heart muscle from the sudden blockage of a coronary artery by a blood clot
- **Perforation** – physical penetration of a vessel or the myocardium
- **Pericardial effusion** – abnormal fluid collection around the heart without hemodynamic compromise
- **Renal failure/dysfunction** – inability of kidneys to perform normal functions
- **Respiratory failure** – inability of the lungs to perform normal functions
- **Seizure** – uncontrolled electrical activity in the brain, which may produce a physical convulsion, minor physical signs, thought disturbances, or a combination of symptoms
- **Significant Residual Flow** – flow  $> 3$  mm jet into the LAA
- **Stroke** – an acute episode (lasting  $> 24$  hours) of focal or global neurological dysfunction caused by brain, spinal cord, or retinal vascular injury as a result of hemorrhage or infarction. Strokes are characterized as follows:
  - **Ischemic Stroke**: an acute episode of focal cerebral, spinal, or retinal dysfunction caused by infarction of the central nervous system tissue. Hemorrhage may be a consequence of ischemic stroke. In this situation, the stroke is an ischemic stroke with hemorrhagic transformation and not a hemorrhagic stroke.
  - **Hemorrhagic Stroke**: an acute episode of focal or global cerebral or spinal dysfunction caused by intraparenchymal, intraventricular, or subarachnoid hemorrhage

- **Undetermined Stroke**: an acute episode of focal or global neurological dysfunction caused by presumed brain, spinal cord, or retinal vascular injury as a result of hemorrhage or infarction but with insufficient information to allow categorization as ischemic or hemorrhagic stroke
- **Thrombus Formation** – a blood clot
- **Transient Ischemic Attack (TIA)**– a transient episode (lasting  $\leq 24$  hours) of focal neurological dysfunction caused by brain, spinal cord, or retinal ischemia, *without* acute infarction on brain imaging
- **Valvular regurgitation/insufficiency** – backflow of blood during contraction of the heart; caused by a defective heart valve
- **Vascular access site injury** – damage at vascular access site (e.g., AV fistula, hematoma, and aneurysm)
- **Vessel Trauma/Injury** – traumatic injuries that damage an artery or vein

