## **4.3 Objectives**

### **4.3.1 Primary objectives**

The Amulet observational post-market study has four primary objectives:

1. Assessment of acute (0 - 7 days post procedure) serious adverse events
2. Assessment of late (> 7 days post-procedure) serious adverse events through 2 years
3. Report the percentage of stroke (ischemic), systemic embolism, and cardiovascular death through 2 years
  - Cardiovascular death is defined as (see **Appendix L**) death due to proximate cardiac cause, death caused by non-coronary, non CNS vascular conditions, death from vascular CNS causes, hemorrhagic stroke, ischemic stroke, all procedure related deaths, sudden or unwitnessed death and death of an unknown cause

4. Report the percentage of bleeding events through 2 years

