## **12. STATISTICAL METHODS**

No formal hypothesis will be tested for this observational post-market study. However, point estimates and exact 95% confidence intervals will be provided for the following rates in the study:

- Procedural serious adverse events (0 - 7 days) post procedure or before hospital discharge whichever latest) will be summarized for all subjects as well as stratified by imaging modality used for implanting the device (TOE and ICE)
- Late serious adverse events through 2 years
- Occurrence of ischemic stroke , systemic embolism and cardiovascular death through 2 years
- Occurrence of bleeding (including hemorrhagic stroke) events through 2 years

Data collected on the following objectives will also be reported:

- Technical success (secondary objective)
- Procedural success (secondary objective) - This objective will be summarized for all subjects as well as stratified by imaging modality used for placement of the device (TOE and ICE)
- OAC usage through 2 years (secondary objective)

- Serious Adverse Events – this may include, but is not limited to:
  - Significant bleeding events (e.g. cardiac tamponade, central nervous system (CNS) bleeding, and any bleeding related to the device or procedure that necessitates an operation)
  - Endocarditis
  - Device embolization (summarized by those that can be snared, and those that require surgical intervention)
  - Thrombus on device
  - All strokes
  - Transient ischemic attacks
  - Systemic embolism
  - Cardiovascular death
- Closure at procedure and 1-3 months post implant
  - The echo core lab's adjudication of residual flow will be used for this analysis. The following guidelines will be used:
    - None – No color flow jet in or out of the LAA
    - Small leak: < 3 mm diameter jet by color flow Doppler
    - Medium leak: 3-5 mm diameter by color flow Doppler
    - Large leak: > 5 mm diameter jet by color flow Doppler

Other variables may be summarized as deemed appropriate. The numerator for all rates will be the number of subjects who experience the corresponding event. The denominator for all rates will be subjects who experience the corresponding event plus all other subjects who achieve 2-years of follow-up.

Version 9.0 or higher of the SAS® statistical software package or other widely accepted statistical software will be used to provide all statistical analyses. Unless otherwise stated, attempts will not be made to adjust for multiple comparisons.

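### Short episodes with infarction on imaging have no settled class under the stroke and TIA definitions, and non-fatal undetermined strokes are named in neither objective 3 nor objective 4

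*Protocol*

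**What the plan says.** Section 8.1 of the protocol gives the event definitions used in the study.

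- **Stroke** (the heading): "an acute episode (lasting $> 24$ hours) of focal or global neurological dysfunction" from a vascular injury, with no imaging alternative to the duration test.
- **Sub-types** are introduced with "Strokes are characterized as follows". Ischemic stroke is "an acute episode of focal cerebral, spinal, or retinal dysfunction caused by infarction of the central nervous system tissue", with no duration stated.
- **Undetermined stroke** is a third class, for a presumed vascular injury "but with insufficient information to allow categorization as ischemic or hemorrhagic stroke".
- **TIA** lasts 24 hours or less and is an episode "of focal neurological dysfunction caused by brain, spinal cord, or retinal ischemia, *without* acute infarction on brain imaging".

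The same section requires specialist and neuroimaging confirmation of any stroke or TIA. Once one is confirmed, it calls for a TOE and a modified Rankin score at 90 days.

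Among strokes, primary objective 3 (Section 4.3.1) counts the ischemic type only, together with systemic embolism and cardiovascular death. Section 12 analyses objective 4 as "Occurrence of bleeding (including hemorrhagic stroke) events through 2 years". Objectives 1 and 2 cover serious adverse events of any type; the first reads "Assessment of acute (0 - 7 days post procedure) serious adverse events" and the second takes the later period to 2 years. Section 12 also lists strokes of every type among the serious adverse events that may be reported.

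**The concern.** The definitions do not divide the cases cleanly. Duration separates stroke from TIA, but infarction also removes a case from TIA, and nothing in the stroke heading takes it back. The required neuroimaging is the test that will find infarcts in short episodes, so the conflict should be expected in practice.

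Objective 3 is the primary objective closest to the device's stated purpose, which is preventing embolization of thrombus from the appendage. The study has no comparator and tests no hypothesis, so the reported percentage is the result, and its case definition should not be open to two readings. Classification also affects data capture: if an episode counts as neither stroke nor TIA, the follow-up imaging and 90-day disability score may not be collected, and later reclassification cannot recover them.

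The undetermined class raises a separate, smaller question. The protocol defines it but assigns it to neither of the two event-specific primary rates.

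**Working it through.** The protocol states no expected stroke rate, sample size derivation or power, so there is no figure to reproduce. The check is a classification of cases against the wording.

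**Step 1. Duration against infarction (Section 8.1).**

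- At most 24 hours, no infarct: TIA.
- More than 24 hours, infarct: ischemic stroke.
- At most 24 hours, infarct: not TIA, because infarction excludes it. Not stroke under the heading, because of the duration limit. Ischemic stroke if the sub-type is read alone.

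In the third case, if the limit carries down to the sub-types, an infarct-proven event has no class. If it does not, the sub-type admits events that its own heading excludes. Such a case cannot enter objective 3 as systemic embolism either, because the embolic event definition is confined to organs outside the central nervous system.

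**Step 2. Undetermined strokes against the primary objectives (Sections 4.3.1 and 12, Appendix L).**

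- Non-fatal: objective 1 or 2 if serious; not objective 3, which takes ischemic strokes; not named in the objective 4 analysis, which takes hemorrhagic strokes.
- Fatal: objective 1 or 2, and can enter objective 3 as cardiovascular death, which includes vascular CNS deaths and deaths of unknown cause.

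Section 12 builds each denominator from subjects with the event plus all others who reach 2 years. A subject with a non-fatal undetermined stroke who reaches 2 years, and has no other qualifying event, therefore counts as event-free in objectives 3 and 4.

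**Step 3. Illustration of size (all inputs assumed).** Take n = 1000 evaluable subjects, all remaining in the denominator; a true 2-year rate of 2%, 4% or 6%; and 10% or 30% of events missed. The observed count is x = (true events) × (1 − share missed). The exact 95% limits are the Clopper-Pearson values: lower = 2.5% quantile of Beta(x, n − x + 1), upper = 97.5% quantile of Beta(x + 1, n − x).

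- 20 true events, 2.0% (1.23 to 3.07): 18 gives 1.8% (1.07 to 2.83); 14 gives 1.4% (0.77 to 2.34).
- 40 true events, 4.0% (2.87 to 5.41): 36 gives 3.6% (2.53 to 4.95); 28 gives 2.8% (1.87 to 4.02).
- 60 true events, 6.0% (4.61 to 7.66): 54 gives 5.4% (4.08 to 6.99); 42 gives 4.2% (3.04 to 5.64).

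With 10% missed, the reported rate stays inside the interval around the true count. With 30% missed, it falls below that interval at 4% (2.8 against 2.87) and at 6% (4.2 against 4.61), but not at 2% (1.4 against 1.23). These lines show only how sensitive the rate is to the share missed; they do not estimate that share.

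**The case against.** The strongest reply is that objective 3 uses the term ischemic stroke, and that sub-definition has no duration limit. Excluding infarction from TIA points the same way: whoever wrote it presumably meant short episodes with infarction to be strokes. A reader might infer from the heading that such events are certainly left out; the text does not support that. What stands is that the sub-type is presented as a kind of an event that must last more than 24 hours, and no rule says which wording prevails.

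A reader might also infer that undetermined strokes enter no primary objective. They do enter one: objectives 1 and 2 take them if serious, and strokes of every type are listed for serious adverse event reporting. Nor does a stroke fatal within 24 hours escape objective 3, since such deaths fall under cardiovascular death in Section 4.3.1 and Appendix L.

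Keeping objective 3 to confirmed ischemic strokes is a legitimate choice. Some undetermined strokes will be hemorrhagic, so counting all of them as ischemic in the main analysis could overstate the rate. Their handling could also properly sit in an analysis plan that is not shown. This is why only a sensitivity line is suggested.

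The Clinical Events Committee (Section 13.2) is charged with refining event definitions and could close the gap. That remit is general, however, and the rule is not written. On data capture, the Synopsis lists the TOE and Rankin scale under suspected events, so failure to collect them is possible rather than certain; the body of the protocol ties both to confirmation.

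**Conclusion.** The inconsistency in Section 8.1 is real and rests on the protocol's wording alone. An episode of 24 hours or less with infarction is outside both stroke and TIA if the duration limit carries down, and has no settled class otherwise. Applied literally, the limit can only lower the ischemic stroke component of objective 3. It is a possible undercount, not a demonstrated one, because the other reading counts these events.

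It also holds that non-fatal undetermined strokes are named in neither objective 3 nor the objective 4 analysis. This is a narrower matter, since they remain visible in objectives 1 or 2 if serious.

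The size cannot be computed from the documents, which give neither a stroke rate nor the share of short episodes with infarction or of undetermined strokes. Any percentage depends on assumed inputs, as in the illustration. Confidence is high in the conflict of wording and low in how many events it would affect.

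**What to change.** In Section 8.1, define stroke as a deficit lasting more than 24 hours, or a deficit of any duration with imaging or autopsy evidence of a corresponding acute infarction or hemorrhage. Keep TIA as 24 hours or less without such evidence. This settles the class of short episodes with infarction and makes them a confirmed stroke for the follow-up assessments.

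In Section 12, leave objective 3 as it is and add one sensitivity line that counts undetermined strokes as ischemic.

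The cost is one definition and one analysis line, ideally fixed before adjudication begins. No extra subjects or tests are needed to classify events, because neuroimaging is already required to confirm a stroke or TIA. The downside is that the reported stroke rate may rise slightly.
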